## Abstract

Adolescent-onset depression is a prevalent and debilitating condition commonly associated with treatment refractory depression and non-response to first-line antidepressants. There are, however, no objective tests to determine who may or may not respond to antidepressants. As depressed adolescents are especially vulnerable to the lifelong consequences of ineffectively-treated depression, it is critical to identify neurobiological predictors of treatment non-response in this population. Here, we describe the scientific rationale and protocol for the Teen Inflammation Glutamate Emotion Research (TIGER) study, a prospective 18-month investigation of 160 depressed adolescents who will be assessed before and after treatment with selective serotonin reuptake inhibitors. TIGER will be using ultra-high field imaging to test the effects of acute stress and antidepressant treatment on inflammatory and glutamatergic processes hypothesized to underlie depression maintenance. Results from this work will motivate future studies testing alternative therapeutics for depressed adolescents at risk for treatment resistant depression. ClinicalTrials.gov Identifier: NCT05329441.

## Introduction

1

Depression is highly debilitating and prevalent among adolescents. Adolescent-onset depression, compared to adult-onset depression, has been associated with longer, more severe, and more recurrent depressive episodes which are often unresponsive to treatment (Clayborne et al., 2019; Johnston et al., 2019; Maalouf et al., 2011). In 2020, 4.1 million adolescents, aged 12–17 years old, were estimated to have experienced at least one major depressive episode, with 41.6% of adolescents in the U.S. receiving treatment in the same year (National Institute of Mental Health, 2022). Alarmingly, up to 40% of adolescents with depression do not respond to first-line antidepressant treatment (i.e., selective serotonin reuptake inhibitors [SSRIs]) (Miller and Campo, 2021; Vitiello et al., 2011), herein termed treatment-non response (TNR). TNR is typically defined as an insufficient reduction (<50%) in clinical depressive symptoms after one adequate treatment trial (i.e., therapeutic dose for at least 8 weeks; (Birmaher and Brent, 2007; Nierenberg and DeCecco, 2001). Ineffectively treated depression often results in a cascade of chronic interpersonal and health difficulties throughout the lifespan that are associated with devastating outcomes, including cardiovascular disease and suicide (Dunn and Goodyer, 2006; Naicker et al., 2013).

Thus, there is a clear need to understand why a substantial portion of adolescents with depression do not respond to first-line antidepressant treatment and what neurobiological pathways may be contributing to TNR to SSRIs. Addressing this critical knowledge gap will equip clinicians and scientists with the means to improve response rates, reduce the number of ineffective treatment trials, and lay the foundation for developing more targeted and effective therapeutics that will promote health outcomes in a young and vulnerable population.

Several specific clinical risk factors, such as earlier age of depression onset, exposure to childhood trauma, and a greater number of psychiatric comorbidities, have been associated with TNR to SSRIs in depressed adolescents (Miller and Campo, 2021; Vitiello et al., 2011; Dunn and Goodyer, 2006; Curry et al., 2011; Dwyer et al., 2020; Emslie et al., 2010). However, to date, there are no objective diagnostic tests indicating which depressed adolescents may respond effectively to first-line SSRIs. Furthermore, depressed adolescents who may respond to SSRI treatment initially may still vary in their time to remission; in fact, up to 80% of depressed adolescents who are treated with SSRIs experience recurrence within two years (Vitiello et al., 2011; Dunn and Goodyer, 2006; Curry et al., 2011; Dwyer et al., 2020; Emslie et al., 1997, 2010; Burcusa and Iacono, 2007). Given the clear heterogeneity in response to SSRI treatment—and in clinical course more generally—it is likely that there are distinct neurobiological mechanisms and/or predictors that underlie subgroups of depressed adolescents defined on the basis of their illness trajectories. In this context, understanding the processes involved in the maintenance of depression is critical for identifying the neurobiological mechanisms of TNR and for improving treatment response and clinical outcomes.

Sustained threat to stress—particularly social stressors characterized by interpersonal conflict—has been implicated as a major risk factor for the onset and maintenance of depression in adolescents (Hammen, 2009). The chronic and compounding nature of these stressors, and how they diminish self-worth, may explain why they are more predictive of depressive episodes and symptoms compared to exposure to other life stressors (Kautz et al., 2020; Ojha et al., 2022; Slavich et al., 2020; Vrshek-Schallhorn et al., 2015; Sheets and Craighead, 2014; Stroud et al., 2011). There is now consistent evidence that there are bidirectional associations between inflammation and depressive symptoms among adolescents (Mac Giollabhui et al., 2021; Moriarity et al., 2020), with compelling theoretical models that outline how exposure to social stressors trigger the same neuroimmune pathways that govern the detection and behavioral responses to pathogens and bodily injuries (Miller and Raison, 2016; Slavich and Irwin, 2014). These stress responses include increased inflammatory signaling in the periphery that ultimately impact multiple pathways in the central nervous system. Specifically, pro-inflammatory cytokines facilitate the release of enzymes that constitute the kynurenine pathway, resulting in the production of neurotoxic metabolites such as quinolinic acid, which bind to N-methyl-D-aspartate (NMDA) receptors, stimulating the release of glutamate (Guillemin et al., 2001; Miller, 2013). Additionally, several cytokines, including tumor necrosis factor-alpha (TNF-α), have been shown to directly compromise structural integrity of astrocytes (which play an important role in reuptake of extracellular glutamate), and reduce the expression of glutamate transporters on oligodendrocytes (Haroon et al., 2017). Over time, the neuroexcitoxic effects of excessive glutamate ought to lead to observable alterations (e.g., decreased gray matter morphometry and white matter microstructure) in brain circuits relevant to the detection and regulation of social stress.

More recently, this confluence of inflammation and glutamate from the lens of stress biology has been applied to our understanding of adolescent depression. Specifically, our group has reported evidence that higher levels of inflammation are associated with higher levels of glutamate in the anterior cingulate cortex in depressed adolescents (Ho et al., 2021), and that higher levels of inflammation are also associated with lower white matter connectivity in fronto-cingulate-limbic tracts (i.e., anterior segments of the corpus callosum (Ho et al., 2022a). Prior work has also shown that functional and structural alterations in fronto-cingulate-limbic circuity—including the anterior cingulate cortex, ventromedial prefrontal cortex, amygdala, and hippocampus—are robust neurophenotypes of adolescent depression (Haroon et al., 2017; Connolly et al., 2013, 2017; Ho et al., 2014, 2015, 2017, 2022b; Kaiser et al., 2015; Kerestes et al., 2013; LeWinn et al., 2014; Miller et al., 2015; Mulders et al., 2015). Interestingly, animal models indicate that inflammation may influence these depression-relevant brain circuits (Miller, 2013; Felger, 2018). Nevertheless, it is unclear whether excessive glutamate is a mechanism by which higher levels of stress-related inflammation may contribute to depression maintenance (or recurrence) and the extent to which these processes are predictive of treatment response to SSRIs.

Here, we outline the rationale and protocol for the Teen Inflammation Glutamate Emotion Research (TIGER) study (R01MH127176; NCT05329441), which seeks to address important gaps in our understanding of how glutamate may explain how peripheral inflammation contributes to TNR and longer-term clinical outcomes in depressed adolescents. The current study will be the first in the field to mechanistically examine the roles of inflammation and glutamate on biobehavioral systems related to sustained threat to social stress, and how those processes contribute to TNR and depression trajectories in adolescents. Leveraging ultra-high field imaging at 7T provides the opportunity to also reliably assess other metabolties, such as γ-aminobutyric acid (GABA), in notoriously difficult corticolimbic regions by providing more reliable localization for regions of interest, improved spectral resolution, and more accurate metabolite quantification (Henning, 2018; Ladd et al., 2018; Lally et al., 2016). Our multimodal results are expected to motivate future studies testing alternative therapeutics for depressed adolescents at risk for treatment resistant depression. Below, we summarize information regarding study aims, participant eligibility/inclusion, the study design, and general methodological procedures.

## Study aims & hypotheses

2

In Aim 1, we will establish whether psychosocial stress increases levels of peripheral inflammation and levels of glutamate in fronto-cingulate-limbic circuits in adolescents with depression.

In Aim 2, we will define TNR based on whether depressed adolescents exhibit at least a 50% reduction in CDRS-R scores after 12 weeks of SSRI treatment. We will compare TNR versus non-TNR groups on TSST-related changes to inflammatory cytokines and glutamate. We will also test whether TSST-related changes in glutamate before and after SSRI treatment mediate the associations between TSST-changes in cytokines at baseline and TNR status (binary outcome). We will also explore models using depression severity as dimensional outcomes instead. We hypothesize that compared to non-responders, responders will show greater stress-induced increases in cytokines and glutamate, as well as stronger positive associations between cytokines and glutamate in threat neurocircuitry.

In Aim 3, we will characterize 18-month trajectories in adolescent depression from behavioral, inflammatory, and neural indicators of threat to social stress. Seven repeated clinical assessments over 18 months will support identifying depression trajectory subgroups (e.g., persistent depression, gradual remission, etc). For binary outcomes (diagnosis of depression), we will use information from clinical interviews to determine remission, relapse, or recurrence status at each timepoint. For dimensional outcomes, we will use symptom severity scores. We hypothesize that increased levels in indicators of sustained threat before and after SSRI treatment, as well as severity of past and ongoing life stress, will predict increased likelihood of experiencing chronic and unremitting depression over 18 months.

For all of the statistical analyses testing these hypotheses, potential demographic (e.g., age, gender), clinical (e.g., age of depression onset, number of comorbidities, presence of childhood trauma), or biological (e.g., percentage of gray matter in MRS voxel) covariates will be included if they are correlated with our outcome variables*.* Statistical significance will be set at α = 0.05. We will apply false discovery rate (FDR) correction as appropriate. In all simulation analyses for estimating sample size based on 1-β = 0.8, effect sizes (*r* or η2 or mean ± SD) were based on preliminary data or cited literature. For the hypotheses in Aims 2 and 3 that require logistic ridge regression analysis, we plan to sample 90% data as the training set and 10% as the testing set across 10 iterations; power was therefore calculated based on 90% of the sample after accounting for attrition (*N* = 108). We will put in rigorous effort to minimize missing data, including scheduling sessions around families’ availability, repeating scans when data were not useable due to movement or scan/user error, and providing bonus incentives for completing all follow-up assessments. For all longitudinal analyses, we will use flexible modeling approaches that allow individuals who provide at least one assessment to be included in our estimation of the effects of interests.

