### Study design

3.3

160 treatment-seeking depressed adolescents who meet includion criteria will complete study procedures every 3 months for 18 months (7 timepoints total). The first assessments of this 18-month study capture the pre-SSRI period (T1) and after 12 weeks of the SSRI (T2). Both T1 and T2 will consist of two distinct visits (Visit 1, V1, and Visit 2, V2), spaced approximately 1–2 weeks apart (see Fig. 1). At V1, we will administer clinical interviews (and at T1V1 we will determine final study eligibility as we will review exclusionary criteria) and self-report surveys to capture symptomatology and clinical history including treatment information (this is relevant mostly at T1). At V2, we will assess peripheral measures of pro-inflammatory cytokines and glutamate in fronto-cingulate-limbic circuits utilizing ultra-high field imaging with a 7T MR scanner before and after a social stress paradigm. Finally, every 12 weeks thereafter through 18 months (T3 to T7), we will administer brief clinical interviews and self-report surveys in order to collect information on depression symptoms and diagnosis in order to characterize, and identify predictors of, trajectories of depression.

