**Fig. 1 fig1:**
[figure not shown]
**Study design for TIGER.** TIGER will be an 18-month longitudinal study consisting of seven timepoints, each 12 weeks apart. The first two timepoints (T1, pre-SSRI treatment, and T2, post-SSRI treatment) will consist of two visits each: visit 1 (V1) will comprise clinical evaluations and self-report questionnaires and visit 2 (V2) will consist of multimodal neuroimaging (see Table 1) and biospecimen collection. After T2, participants will complete five follow-up assessments every 12 weeks (T3-T7), which will consist of clinical assessments of depression, updated treatment and health history information, and completion of self-report questionnaires.

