### Trier Social Stress Task (TSST)

3.6

A modified version of the Trier Social Stress Task (TSST) will be administered at T1V2 and T2V2. This adapted TSST involves no deception and follows procedures similar to those used by our group in adolescent populations (Ho et al., 2020; Kircanski et al., 2019; Miller et al., 2019). Following the first set of brain imaging acquisitions and the first blood sample collection, participants will be instructed by an experimenter that they will be completing a stress test. There will be two versions of the stress test: a five-minute arithmetic task or a five-minute speech task (regardless of the task, participants will be given 5 minutes of prep time beforehand). Participants will be randomly assigned one of the two stress tests at T1 and will be administered the second stress test at T2 to minimize habituation with repeated testing and ensuring that the order of the two tests are counterbalanced across the sample.

Upon arrival to the session, before, and after the TSST, participants will provide ratings of ten mood states (*Excited, Afraid, Confused, Sad, Energetic, Angry, Happy, Tired, Tense)* based on the Positive and Negative Affect Schedule (PANAS; Crook et al., 1998) on a visual analogue scale from 0 to 10. These ratings will be used as tertiary outcome measures of behavioral responses to social stress. During administration of the TSST, we will also collect saliva samples repeatedly to explore changes in stress hormones before and after an acute stressor. Five saliva samples, each collected approximately 10 minutes apart, will be collected using the SalivaBio Oral Swab Method (Salimetrics, LLC) during the TSST protocol, from which we plan to assay cortisol production. After completing the TSST, participants will complete the remaining scans and provide a secondary blood sample approximately 120 minutes after the first blood sample and then provide a final saliva sample. Additionally, it is possible that secondary stress and anxiety may affect cytokine and CRP levels at Time 1, as this will be the first time most of the participants will have undergone an MRI scan; however, our primary measures of inflammation and glutamate are *within-person differences* before and after the TSST. We will also consider using the PANAS ratings of mood states as covariates in sensitivity analyses.

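### Aim 2 tests post-SSRI (T2V2) glutamate change as a mediator of TNR, but it is measured after TNR is rated, or at best with it, so direction cannot be identified; Aim 3 has a smaller version of the problem

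*Protocol article*

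**What the plan says.** All references are to the protocol article.

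- **Outcome of Aim 2** (Study aims & hypotheses): "we will define TNR based on whether depressed adolescents exhibit at least a 50% reduction in CDRS-R scores after 12 weeks of SSRI treatment".
- **Mediation model of Aim 2** (same section): the plan will test whether "TSST-related changes in glutamate before and after SSRI treatment mediate the associations between TSST-changes in cytokines at baseline and TNR status". The mediator thus includes a pre-treatment and a post-treatment measurement.
- **Visit order** (Study design): "Both T1 and T2 will consist of two distinct visits (Visit 1, V1, and Visit 2, V2), spaced approximately 1–2 weeks apart". On content, "At V1, we will administer clinical interviews", and "At V2, we will assess peripheral measures of pro-inflammatory cytokines and glutamate in fronto-cingulate-limbic circuits". The Fig. 1 legend repeats the split: "visit 1 (V1) will comprise clinical evaluations and self-report questionnaires and visit 2 (V2) will consist of multimodal neuroimaging". The section on the TSST places the stress task at T1V2 and T2V2.
- **Aim 3** (Study aims & hypotheses): subgroups are to be identified from the seven clinical assessments over 18 months. The hypothesis is that "increased levels in indicators of sustained threat before and after SSRI treatment", together with life stress, will predict a chronic, unremitting course over those 18 months.

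The article describes no landmark at T2, no restriction of T2V2 indicators to later outcomes, and no separate handling of the T2V2 mediator.

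**The concern.** A mediation model assumes that the exposure acts on the mediator and the mediator then acts on the outcome. Here the exposure is baseline cytokine change and the outcome is CDRS-R change over about 12 weeks. Part of the mediator is read at the end of that period or just after it. Having responded, or not, may itself alter glutamate reactivity at T2V2. The Discussion treats an effect of SSRIs on glutamate as an open question, so a post-treatment shift is plausible within the study's own framework.

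If the arrow runs from response to glutamate, the model still returns a non-zero indirect effect, and it would be read as support for the study's central mechanism. In Aim 3, a T2V2 indicator would be credited with predicting a course of which part was already observed.

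**Working it through.** **1. Timeline for Aim 2.** Inputs: timepoints 12 weeks apart (Fig. 1 legend), and V1 before V2 by 1–2 weeks (Study design). With T1V1 at week 0:

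| Event | Approximate week |
|---|---|
| T1V1: clinical rating | 0 |
| T1V2: cytokine and glutamate change | 1–2 |
| T2V1: clinical rating (TNR, by inference) | 12 |
| T2V2: cytokine and glutamate change | 13–14 |

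T1V2 glutamate precedes the TNR rating by about 10–11 weeks (12 − 2 to 12 − 1), or about 12 if the interval is counted from an SSRI start after T1V2. T2V2 glutamate follows the rating by 1–2 weeks. Only the T2V2 part is out of order.

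**2. Timeline for Aim 3.** T1 to T7 spans 6 × 12 = 72 weeks. T2V2 falls at 13/72 = 18% to 14/72 = 19% of that span. Two of the seven assessments (T1, T2) precede it and five (T3–T7) follow. Every participant meets criteria for a depressive disorder at entry (Study eligibility), so T1 diagnosis separates nobody. For diagnostic outcomes the overlap is in effect T2 alone; for severity it is T1 and T2.

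**3. Size of a spurious indirect effect (illustration).** The article gives no figure to reproduce here. Assume standardised linear variables: cytokine change X acts on outcome Y with correlation r, Y acts on T2V2 glutamate M with correlation c, and M has no effect on Y. Then:

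- a (X to M) = c·r
- b (M to Y given X) = (c − a·r)/(1 − a²) = c(1 − r²)/(1 − c²r²)
- share attributed to mediation = a·b/r

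For r = 0.3, c = 0.5: a = 0.150; b = 0.455/0.9775 = 0.465; a·b = 0.070; share = 0.070/0.3 = 23%.

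| r | c = 0.3 | c = 0.5 |
|---|---|---|
| 0.2 | 8.7% | 24.2% |
| 0.3 | 8.3% | 23.3% |
| 0.4 | 7.7% | 21.9% |

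The true share is zero in every cell. The values of r and c are assumptions.

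**4. False-positive rate with a binary outcome (illustration).** TNR is binary, so the same structure was simulated with a logistic outcome model. The TNR rate was about 40% (Discussion). N was 108, the figure given for the ridge models under Study aims & hypotheses; it equals 160 × 0.75 × 0.90 if attrition is 25%, a rate the article does not state. There were 1000 runs per cell, with two-sided 5% tests and no true mediation.

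| Correlation of TNR with T2V2 glutamate | Log odds ratio of X on TNR | Joint significance | Sobel |
|---|---|---|---|
| 0 | 0.5 / 0.8 / 1.2 | below 1% | 0% |
| 0.3 | 0.5 / 0.8 / 1.2 | 10% / 18% / 22% | 4% / 7% / 8% |
| 0.5 | 0.5 / 0.8 / 1.2 | 22% / 45% / 69% | 16% / 35% / 58% |

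With N = 120 the rates are similar or slightly higher.

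**The case against.** **The CDRS-R visit is inferred.** The article never states that the CDRS-R is rated at T2V1. The inference rests on its being clinician-rated and on V1 being the clinical visit. This stands as a caveat. A T2V2 rating would make mediator and outcome concurrent, which still leaves direction unidentified.

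**Order of measurement is not causal order.** A reader might infer that a variable measured after the outcome cannot be its mediator. That is too strong. TNR is a change over 12 weeks, and the mediator may be meant as the shift in reactivity from T1 to T2 over nearly the same interval. A true mediating process could be running then. What stands is narrower: the design cannot separate that process from its reverse.

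**Aim 3 may be handled elsewhere.** The article also plans status at each timepoint and dimensional scores, and a landmark could sit in a fuller plan. This is fair, and inflation in Aim 3 has not been quantified. But the stated hypothesis uses post-SSRI indicators to predict the whole 18 months, so the wording needs correcting.

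**The illustration uses assumed inputs.** This is correct. With a correlation of 0.3, the Sobel rate is close to nominal; the large error rates need a correlation of 0.5 and a sizeable cytokine effect.

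**Two further readings are not supported.**

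- Within T1V2, a participant will "participants will complete the remaining scans and provide a secondary blood sample approximately 120 minutes after the first blood sample". A reader might infer that the cytokine exposure follows the glutamate mediator. The Discussion explains the draw time as chosen to capture the acute stress response, and a later draw does not show a later response.
- A reader might also infer that the Discussion's promise of predictors of non-response fails. It does not say that T2 biomarkers are those predictors, and T1V2 measures can serve.

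**Conclusion.** The point holds for the T2V2 mediator in Aim 2. By the article's own visit schedule it follows the TNR rating by 1–2 weeks, or is concurrent with it, and an indirect effect through it cannot be distinguished from an effect of response on glutamate. Under assumed correlations, 8%–24% of the cytokine effect would be labelled mediation when none exists. These figures show the direction and a possible scale of the error, not its size in this study.

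The T1V2 mediator is correctly ordered relative to TNR. The comparison of TNR and non-TNR groups on T2V2 reactivity is sound as an association.

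For Aim 3 the fault is partial: five of seven assessments follow T2V2, and the overlap is the T2 rating, plus T1 where severity is used.

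**What to change.** 1. Limit the TNR mediation model to the T1V2 glutamate change, and report the result as an indirect association.
2. Report T2V2 biomarkers as correlates of TNR, not as mediators or predictors of it.
3. In Aim 3, use T2V2 indicators only to predict severity or diagnosis at T3–T7, conditional on T1 and T2 CDRS-R. Use T1V2 indicators for outcomes from T2 onward, conditional on T1 severity. That leaves five of seven assessments as outcome for T2V2 indicators and six of seven for T1V2 indicators.

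The cost is analysis wording; visits, procedures and sample size do not change. The scientific price is that the T2 mechanism claim becomes an association. The change should be made before the data are analysed, because a later choice between T1 and T2 mediators would look driven by results.

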### Measures of depression

3.4

We will be administering the K-SADS-PL (Kaufman et al., 1997) for assessing Axis I disorders in all study participants (as assessments for depressive disorders do not meaningfully differ between K-SADS-PL and similar instruments designed for adults such as the Structured Clinical Interview for DSM Disorders). The K-SADS-PL will be used at baseline to determine depression diagnosis according to the DSM-5 and study eligibility (as potential participants with a history of mania, psychosis or who have current substance use disorders will be excluded from the study). Depression diagnosis will also be used as an outcome measure to determine remission versus recurrence throughout the study period. We will also administer a modified version of the Family Interview for Genetic Studies (FIGS; Maxwell, 1992) at T1 in order to exclude potentially depressed participants who have first-degree relatives with mania or psychosis. The study group will convene weekly to discuss any ambiguous codes.

To assess depression severity dimensionally, we will administer the Children's Depression Rating Scale-Revised (CDRS-R), a 17-question, clinician-rated scale assessing dimensional scores of depression severity, and the Reynolds Adolescent Depression Scale, 2nd Edition (RADS-2), which is a 30-item self-report questionnaire assessing depression severity for the past two weeks. Both scales have been widely used in clinical trials and research studies of adolescent depression demonstrate sensitivity and reliability in assessing depression symptoms across time (Poznanski et al., 1984; Reynolds, 2010). Additionally, we will administer the Patient Health Questionnaire 9 (PHQ-9), a 9-item screener for depression that is commonly used in clinic and research settings for adults and adolescents and for assessing rapid symptom changes (Kroenke et al., 2001).

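### The post-treatment glutamate change does not precede the response it is meant to mediate, so the T2 leg of the Aim 2 mediation does not identify direction

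*Protocol article*

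**What the plan says.** **Mediation model** (Study aims & hypotheses, Aim 2). The study will test whether "TSST-related changes in glutamate before and after SSRI treatment mediate the associations between TSST-changes in cytokines at baseline and TNR status". The exposure is the baseline cytokine change under the stress test (TSST). The mediator is the TSST glutamate change at both T1 and T2. The outcome is binary TNR status.

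**Outcome.** Aim 2 will "define TNR based on whether depressed adolescents exhibit at least a 50% reduction in CDRS-R scores after 12 weeks of SSRI treatment". Section 3.3 places the end of the 12 weeks at T2. Section 3.4 describes the CDRS-R as "a 17-question, clinician-rated scale assessing dimensional scores of depression severity" and does not assign it to a visit.

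**Visits** (section 3.3). "Both T1 and T2 will consist of two distinct visits (Visit 1, V1, and Visit 2, V2), spaced approximately 1–2 weeks apart". On content: "At V1, we will administer clinical interviews" and "At V2, we will assess peripheral measures of pro-inflammatory cytokines and glutamate in fronto-cingulate-limbic circuits". The legend of Fig. 1 agrees: "visit 1 (V1) will comprise clinical evaluations and self-report questionnaires and visit 2 (V2) will consist of multimodal neuroimaging". Section 3.6 places the TSST at T1V2 and T2V2.

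No passage limits the TNR mediation to T1 glutamate, and none addresses the possibility that the effect runs from response to glutamate.

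**The concern.** A mediator has to act before the outcome it explains. The T2 glutamate change is measured at the end of treatment, when the participant has already improved or not, and improvement may itself change stress reactivity. The Discussion asks separately whether SSRIs affect glutamate regardless of TNR status, so change in glutamate during treatment is a live possibility within the study itself.

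If response shifts glutamate, a standard mediation analysis can return a significant indirect effect although glutamate has no effect on response. The Introduction gives as the study's purpose to learn whether glutamate explains how peripheral inflammation contributes to TNR. A consequence of recovery could then be reported as a mechanism of non-response.

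**Working it through.** **1. Order of events**

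| Step | Event | Source |
|---|---|---|
| 1 | T1V2: TSST, cytokines, glutamate | 3.3, 3.6 |
| 2 | 12 weeks of SSRI | 2, 3.3 |
| 3 | T2V1: clinical interviews; CDRS-R by inference | 3.3, Fig. 1, 3.4 |
| 4 | about 1–2 weeks later, T2V2: TSST, glutamate | 3.3, 3.6 |

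If the CDRS-R is at T2V1, the T2 mediator is measured after the outcome. If it were moved to T2V2, the two would be concurrent. Either way the scan does not precede a change accrued over step 2. A T1-to-T2 difference in glutamate also uses the T2V2 scan, so it has the same problem.

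**2. Why the fitted model cannot tell direction**

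Let X be baseline cytokine change, Y be TNR (0/1) and M be T2 glutamate change. Suppose Y affects M and not the reverse: logit P(Y=1|X) = α + βX, and M given Y is normal with mean dY and SD 1. By Bayes' rule

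logit P(Y=1|X,M) = α + βX + dM − d²/2.

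The logistic regression of Y on X and M thus has coefficient d for M, exactly as if glutamate drove TNR with odds ratio exp(d) per SD: exp(0.5) = 1.65, exp(0.8) = 2.23, exp(1.2) = 3.32. M is also associated with X, because X predicts Y and Y shifts M. Both legs of an apparent indirect effect appear with no effect of M on Y.

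**3. Size under assumed effects**

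No figure in the article tests this point. Inputs from the article: TNR rate 40% (Discussion), α = 0.05 and power N = 108 (section 2). As 108/0.90 = 120 and 120/160 = 0.75, the N after attrition is 120, which implies 25% attrition.

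Assumed: the odds ratio (OR) for TNR per SD of cytokine change; the glutamate shift between TNR groups in SD; and a joint-significance test (M on X by least squares, Y on X and M by logistic regression, both p < 0.05). There were 1,000 runs per setting and no effect of M on Y. Entries are the percentage of runs declaring mediation.

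| OR | N | shift 0 | 0.5 | 0.8 | 1.2 |
|---|---|---|---|---|---|
| 1 | 108 | 0.4 | 4.5 | 6.3 | 6.4 |
| 1 | 120 | 0.2 | 2.5 | 5.0 | 4.5 |
| 1.5 | 108 | 0.4 | 4.4 | 10.6 | 14.7 |
| 1.5 | 120 | 0.2 | 4.4 | 11.9 | 17.4 |
| 2 | 108 | 0.5 | 8.6 | 20.0 | 35.6 |
| 2 | 120 | 0.2 | 7.3 | 22.7 | 39.0 |
| 3 | 108 | 0.4 | 9.4 | 36.5 | 64.8 |
| 3 | 120 | 0.1 | 13.3 | 37.5 | 69.1 |

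The simulation error near 5% is √(0.05 × 0.95/1000) = 0.7 percentage points, so the OR 1 rows are compatible with 5% or less.

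A second set of simulations used latent correlations. With a cytokine–TNR correlation of 0.3 and N = 120, the rate was 0.2%, 11% and 35% for response–glutamate correlations of 0, 0.3 and 0.5. With N = 108 it was 0.2%, 7.6% and 32.7%. With a response–glutamate correlation of only 0.1–0.2, it was 0.4% to 3.6% for cytokine–TNR correlations of 0.1 to 0.3. With a cytokine–TNR correlation of 0.1 and a response–glutamate correlation of 0.3, it was 3% to 5%.

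**The case against.** **The CDRS-R visit is not stated.** This stands. Placing it at T2V1 is a fair inference from a clinician-rated scale and a visit reserved for clinical evaluation, but it is an inference. The point does not depend on it, since a same-day rating leaves the two concurrent.

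**A late scan may index an earlier state.** This also stands. A reader might infer that T2 glutamate cannot be a mediator because it was measured after the outcome. The documents do not support that: glutamate may have shifted early in treatment, with T2V2 recording a persisting state. What follows is that direction is not identified, because there is no scan between T1 and T2 to separate the two accounts.

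**The simulations are conditional.** They contain no time variable, so they show what a reverse effect does and not what a gap of 1–2 weeks does. They assume a test the article does not name, and they model neither the ridge regression nor the FDR correction of section 2. A reader might infer that a false mediation finding is likely. That is not shown: with weak links the rate stays at or below about 5%.

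**Much is already planned, and the claims are modest.** Aim 2 already compares TNR groups on TSST-related glutamate change, Aim 3 already uses indicators from after treatment, and the Discussion speaks of preliminary evidence. This lowers the severity. It does not remove the T2 mediator from the stated model.

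**The analysis plan may settle it.** The plan is not shown, but exposure, mediator, outcome and visit order are all fixed in the article. A plan that follows it inherits the problem.

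**Conclusion.** The concern holds for the T2 leg of the Aim 2 mediation and for any T1-to-T2 glutamate difference used as mediator of TNR. A significant indirect effect through T2 glutamate would not support mediation, because the same result arises when response or non-response alters glutamate.

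The size depends on two effects the documents do not give. With no true mediation, the declared rate runs from under 1% to about 35%, and up to 69% in the most extreme setting tried. It clearly exceeds 5% only when baseline cytokine change predicts TNR and response shifts glutamate, each by a moderate amount or more.

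The exploratory dimensional models share the problem if severity is taken at T2. The T1 leg, the group comparisons, Aim 1 and outcomes from T3 to T7 are not affected by it. Severity: should be fixed.

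**What to change.** - In the mediation model with TNR as outcome, allow only the T1 TSST glutamate change as mediator.
- Analyse the T2 glutamate change, or the T1-to-T2 change, by TNR status, and describe it as a correlate or consequence of response.
- Use T2 glutamate as a mediator or predictor only for outcomes from T3 onward, adjusted for T2 severity. Aim 3 comes close to this, but its trajectories draw on all seven assessments, so the restriction needs to be written down.
- State at which T2 visit the CDRS-R that defines TNR is given.

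The cost is rewording before analysis; no new data are needed. The TNR mediation claim narrows to pre-treatment glutamate. That leg keeps a limitation of its own: under section 3.6 the second blood sample follows the remaining scans, about 120 minutes after the first, so the cytokine change is completed after the glutamate it is meant to precede. This should be acknowledged when the T1 result is reported.
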